## Abstract

**Background:**

Moderate to severe osteoarthrosis is the most common indication for Total Hip Arthroplasty (THA). Minimally Invasive Total Hip Surgery (MIS) and computer-navigated surgery were introduced several years ago. However, the literature lacks well-designed studies that provide evidence of superiority of computer-navigated MIS over a conventional THA technique. Hence, the purpose of this study is to compare (cost)effectiveness of computer-navigated MIS with a conventional technique for THA. It is our hypothesis that computer-navigated MIS will lead to a quicker recovery during the early postoperative period (3 months), and to an outcome at least as good 6 months postoperatively. We also hypothesize that computer-navigated MIS leads to fewer perioperative complications and better prosthesis positioning. Furthermore, cost advantages of computer-navigated MIS over conventional THA technique are expected.

**Methods/design:**

A cluster randomized controlled trial will be executed. Patients between the ages of 18 and 75 admitted for primary cementless unilateral THA will be included. Patients will be stratified using the Charnley classification. They will be randomly allocated to have computer-navigated MIS or conventional THA technique. Measurements take place preoperatively, perioperatively, and 6 weeks and 3 and 6 months postoperatively. Degree of limping (gait analysis), self-reported functional status and health-related quality of life (questionnaires) will be assessed preoperatively as well as postoperatively. Perioperative complications will be registered. Radiographic evaluation of prosthesis positioning will take place 6 weeks postoperatively. An evaluation of costs within and outside the healthcare sector will focus on differences in costs between computer-navigated MIS and conventional THA technique.

**Discussion:**

Based on studies performed so far, few objective data quantifying the risks and benefits of computer-navigated MIS are available. Therefore, this study has been designed to compare (cost) effectiveness of computer-navigated MIS with a conventional technique for THA. The results of this trial will be presented as soon as they become available.

## Background

Moderate to severe osteoarthrosis is the most common indication for total hip arthroplasty (THA). Incidence of THA in 2005 was 124 per 100,000 inhabitants (20,281 operations) in the Netherlands [1]. Over the past 40 years, THA has proven to be one of the most successful orthopedic interventions. The 15-year prosthesis survival rate exceeds 90% [2]. Thanks to excellent long-term results and technical improvements, more elderly people who were previously judged to be too old or too sick are considered suitable for THA. Moreover, the number of older adults is increasing [3]. Consequently, a boost will be seen in the demand for THA. Together with the shift toward greater cost effectiveness in healthcare, this growing demand triggers the introduction of potentially cost-saving procedures such as Minimally Invasive Total Hip Surgery (MIS).

MIS was introduced in the orthopedic community several years ago. Compared to the conventional incision technique for THA, a shorter incision is made. Proponents of MIS claim that it results perioperatively in less soft-tissue trauma (smaller skin incision and less muscle damage), reduced blood loss and fewer blood transfusion requirements. Postoperative benefits include less pain, quicker recovery (e.g earlier return to normal gait) and better cosmetic appearance [4-7]. Opponents of MIS argue that it leads to more complications, mainly due to poorer operative visualization of landmarks and vital structures [8]. Among the complications are neurovascular injury, femoral fracture and component malposition, which can result in more wear of the prosthesis. A higher risk for thromboembolism and infection is claimed, due to a longer operation time for MIS.

A solution to the poorer operative visualization is to consider using MIS in combination with computer navigation [7]. Several studies have shown that inaccuracies in prosthesis placement by means of conventional THA techniques can be significantly reduced by using computer navigation [9-11]. Some even hypothesize that MIS in combination with computer navigation will result in better positioning of the prosthesis, compared to conventional THA techniques [12].

In terms of cost effectiveness, MIS enthusiasts claim cost reduction due to earlier discharge from the hospital and sooner return to work, as MIS leads to a quicker recovery [13,14]. Opponents argue a cost increase as specialized equipment (e.g. computer navigation) is needed and operation time is longer [15].

Due to pressure from the industry as well as patients, the orthopedic community has widely embraced MIS. MIS and computer navigation are considered to be potential steps forward in the treatment of THA patients. The orthopedic literature however lacks well-designed studies that provide objective evidence on the effectiveness of computer-navigated MIS, especially in the early postoperative period (first 3 months), when its potential benefits are claimed to be substantial.

Hence, the purpose of this study is to conduct a randomized controlled trial to compare (cost) effectiveness of two THA techniques: computer-navigated MIS and a conventional technique. It is our hypothesis that computer-navigated MIS will lead to a quicker recovery during the early postoperative period (3 months), and to an outcome at least as good at 6 months postoperatively. We also hypothesize that computer-navigated MIS leads to fewer perioperative complications and better prosthesis positioning. From an economic perspective, cost benefits of computer-navigated MIS over conventional THA technique are expected. The present paper reports on the methodological design of the study.

## Methods/design

### Study design

A cluster randomized controlled trial will be conducted. Patients will be stratified into 3 groups based on the Charnley classification, by means of which total hip arthroplasty patients can be subdivided by degree of comorbidity affecting the function of walking. The Charnley classification recognizes three categories. Category A denotes patients with only one hip involved, in whom no other condition interferes with walking. Category B denotes patients with both hips involved but the rest of the body normal and therefore not responsible for any defect in walking. Category C denotes patients with some factors contributing to failure to achieve normal locomotion, such as polyarthritis or rheumatoid arthritis, or cardiovascular or respiratory disability [16]. By using this stratification, the influence of factors other than the THA affecting normal walking will be accounted for.

Within the strata, patients will be randomly allocated to have computer-navigated MIS or the conventional THA procedure by means of cluster randomization to avoid interaction between both patient groups. The random allocation sequence will be computer-generated by an independent planner of the Medical Assessment Office of University Medical Center Groningen (UMCG). The study design, procedures and informed consent are approved by the Medical Ethics Committee of UMCG.

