### Study population

The study will be conducted at the Orthopedic Department of the UMCG. Patients between the ages of 18 and 75 who are admitted for primary cementless unilateral THA due to primary or secondary osteoarthrosis will be included. Patients with inflammatory polyarthritis or with a history of previous surgery on the affected hip will be excluded. Participation in the study is voluntary and patients have to provide informed consent before participation. The inclusion period is planned from March 2007 to May 2008.

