### Measurements

In this study, recovery is operationalized as the proportion of subjects with normal gait (no limping during walking) and as the self-reported functional status and health-related quality of life. Measurements will take place preoperatively (day of admission) and perioperatively, and 6 weeks and 3 and 6 months postoperatively. The amount of limping and self-reported functional status and health-related quality of life will be assessed preoperatively as well as postoperatively. Perioperative complications will be registered. Evaluation of prosthesis positioning will take place 6 weeks and 6 months postoperatively. The economic evaluation will focus on differences in costs between computer-navigated MIS and conventional THA technique. The evaluation will be performed from a societal perspective; costs within and outside the healthcare sector will be registered over a period of 6 months. Demographic data, diagnosis, height, weight and BMI, and ASA and Charnley classifications will also be recorded preoperatively.

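### Allocation is described both as patients within Charnley strata and as by cluster; in a single department the two stated aims conflict as written, and the sample size assumes patients as the unit

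*Protocol article*

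**What the plan says.** The Study design section of the protocol article opens with "A cluster randomized controlled trial will be conducted". It continues: "Patients will be stratified into 3 groups based on the Charnley classification", and gives the purpose: "By using this stratification, the influence of factors other than the THA affecting normal walking will be accounted for". Allocation is then described in one sentence: "Within the strata, patients will be randomly allocated to have computer-navigated MIS or the conventional THA procedure by means of cluster randomization". The reason for clustering is in the same sentence: "by means of cluster randomization to avoid interaction between both patient groups". I read interaction here as contact between patients of the two arms, not as a statistical interaction. An independent planner generates the sequence by computer.

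Four other sections bear on the point:

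- **Study population:** one orthopaedic department, inclusion from March 2007 to May 2008, and "Participation in the study is voluntary and patients have to provide informed consent before participation".
- **Measurements:** Charnley class is recorded preoperatively.
- **Sample size:** 50 per group for the 3-month superiority comparison and 60 per group for the 6-month non-inferiority comparison. The latter gives 132 patients with 10% dropout. No cluster size, intracluster correlation or design effect appears.
- **Statistical analysis:** random effect models are named for the longitudinal analyses, without reference to clusters.

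**The concern.** The allocation sentence names two units. Patients within strata means that each patient is assigned inside his or her Charnley class. Cluster randomisation means that a group of patients is assigned as a whole. Each is tied to its own benefit, and in one department the text does not show how both can be had together.

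Three things depend on the answer: whether the arms are balanced on Charnley class by design, whether contact between the groups is in fact limited, and whether the patients can be treated as independent in the sample size and the analysis.

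There is also a conditional risk. If a cluster's arm becomes known while its later members are still being recruited, inclusion or refusal could depend on the arm. An independently generated sequence does not by itself prevent that.

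**Working it through.** **Step 1. The two possible schemes, set against the two aims.**

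- *A cluster is a group of patients treated together.* This serves the aim of avoiding contact. Such a group will normally contain more than one Charnley class and receives one arm, so patients are not allocated within strata.
- *Clusters are formed inside each class.* This respects the strata. The three classes recruit in the same department over the same months, so clusters in different arms can be open together.

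The article's own figures show how often the second case could arise. March 2007 to May 2008 is 15 months, and 132 / 15 = 8.8 patients a month. Assume equal class shares and clusters of 5 (neither is stated). A within-class cluster then fills in 5 / (8.8 / 3) = 1.7 months, while the other classes are also recruiting. With independent 1:1 allocation of clusters:

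- with three open clusters, all share an arm with probability 2 × (1/2)³ = 0.25, so both arms are present 75% of the time;
- with two open clusters, the probability is 2 × (1/2)² = 0.50, so both arms are present 50% of the time.

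**Step 2. Which unit the sample size uses.** The inputs from the Sample size section are 0.95 in both groups, margin 0.10, significance level 0.05 and power 80%. Taking the level as one-sided:

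n = (1.645 + 0.842)² × 2 × 0.95 × 0.05 / 0.10² = 6.185 × 0.095 / 0.01 = 58.8, so 59 per group.

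The article states 60. That leaves room for a design effect of at most 60 / 58.8 = 1.02. The total follows as 120 × 1.10 = 132; dividing by 0.9 gives 134. The unit is therefore the patient. The 3-month figure of 50 cannot settle the matter, because no control proportion is given. Without a continuity correction, control rates from 0.05 to 0.70 give at most 47. With one, rates of 0.20 or 0.55 give 49, and 0.25 or 0.50 give 52.

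**Step 3. What clustering would do to the 6-month comparison.** With m patients per cluster and intracluster correlation ICC, the design effect is DE = 1 + (m − 1) × ICC. The size per group is 60 × DE, and the total is twice that divided by 0.9. Power at 60 per group is Φ(0.10 / √(0.095 × DE / 60) − 1.645). All values of m and ICC are assumptions.

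| m | ICC | DE | Per group | Total | Power at 60 |
|---|---|---|---|---|---|
| individual | – | 1.00 | 60 | 134 | 0.81 |
| 5 | 0.01 | 1.04 | 63 | 140 | 0.79 |
| 5 | 0.05 | 1.20 | 72 | 160 | 0.74 |
| 10 | 0.01 | 1.09 | 66 | 147 | 0.78 |
| 10 | 0.05 | 1.45 | 87 | 194 | 0.67 |
| 20 | 0.05 | 1.95 | 117 | 260 | 0.56 |

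The totals should be compared with 134, which uses the same dropout formula, and not with 132.

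**The case against.** The strongest reply is that a journal article condenses the protocol, and that the definition of the cluster and the concealment procedure may stand in the full document. That holds for the missing definition, the missing cluster term in the analysis and the timing of release; none of these is a fault in itself. It does not remove the conflict, because both units and both aims appear together in the article and its sample size follows only one of them.

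A reader might infer that the two aims can never be met together. The documents do not support that. Admitting patients by stratum, or balancing clusters on their Charnley mix, could reconcile them; the article describes neither.

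A reader might also infer that the arm is exposed before patients enrol. Nothing says that clusters are assigned in advance, that recruitment follows assignment, or when the planner releases the arm. Consent is required before participation. The risk is therefore conditional.

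Nor does the text promise balance on Charnley class. It says that other influences will be accounted for, and since the class is recorded preoperatively, adjustment in the analysis can do part of that. Any figure for bias from a Charnley imbalance would need class shares and class-specific gait proportions that the article does not give, so none is offered here.

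Finally, the ICC may be small in a single department with standardised anaesthetic, analgesic and physiotherapy protocols. The lower rows of ICC in the table allow for this.

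**Conclusion.** The concern holds as a conflict in the stated design. Allocation within a patient-level stratum and allocation by cluster are both claimed for one department, each with its own purpose, and the text gives no scheme that delivers both. The 6-month sample size treats the patient as the unit.

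The consequence depends on what was meant. If allocation is individual, the sample size is unaffected and the cluster label is wrong. If allocation is by cluster, assumed sizes of 5 to 10 and ICCs of 0.01 to 0.05 raise the requirement from 60 to between 63 and 87 per group (140 to 194 in total), or lower power at 60 per group to between 0.79 and 0.67. These figures rest on a one-sided 0.05 level, equal cluster sizes and the assumed m and ICC. They show a range and do not establish that the trial is underpowered.

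**What to change.** State one scheme in the Study design section and carry it through.

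**If clusters are kept:**
- Define the cluster (what it is, its size and the number of clusters) and allocate it whole.
- Replace allocation within strata by balancing clusters on Charnley mix where possible, and adjust the gait comparison for Charnley class, which is already recorded.
- Restate power in the Sample size section with a design effect under a stated ICC and cluster size.
- Add a cluster term to the models in the Statistical analysis section.
- Have the planner reveal a cluster's arm only after its patients have consented and been Charnley-classified. This need not wait for the baseline measurement on the day of admission.

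**If allocation is individual within Charnley strata:** remove the cluster label from the abstract and the Study design section, and say openly that the two groups may have contact. The 60 per group then stands.

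The cost is mainly wording, plus a release rule for a planner who is already in place. With clusters, theatre planning learns the arm somewhat later, and the stated power may be slightly lower or the sample larger. With individual allocation, the aim of keeping the groups apart is given up.

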### Sample size

It is our hypothesis that computer-navigated MIS will lead to better recovery during the early postoperative period (3 months), and at least as good at 6 months postoperatively. In order to detect a difference of 0.254 in the proportion of subjects with normal gait after 3 months of follow-up with 80% power at a significance level of 0.05 in a one-sided test of a difference between two proportions, two groups of 50 subjects are required. With an expected dropout rate of 10%, a total of 110 patients is needed. At 6 months, the effect of MIS and conventional THA technique on gait (limping) will be compared in a non-inferiority setting. To establish non-inferiority, the lower bound of the 95% confidence interval of the difference between the two treatment groups will be compared with a non-inferiority margin delta. If the whole confidence interval of the difference between the two treatments is smaller than the non-inferiority margin delta, non-inferiority is established. The non-inferiority margin delta is chosen in this study at a value of 0.10, indicating that a difference in proportion of subjects with a normal gait of 0.10 is considered clinically equivalent. To deduce non-inferiority with 80% power at a significance level of 0.05 with expected proportions of subjects with normal gait of 0.95, using a non-inferiority margin delta of 0.10, two groups of 60 subjects are required. With an expected dropout rate of 10%, a total of 132 patients is needed.

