### Statistical analysis

All statistical analyses will be computed using the Statistical Package for the Social Sciences (SPSS, Inc., Version 12.0, 2003, Chicago). Descriptive statistics will be used to describe both research groups. Analysis of variance (ANOVA) and chi-square procedures will be used to evaluate between-group differences at baseline. Random effect models will be applied for longitudinal analyses. In order to enable statistical conclusions on differences in (skewed distribution of) costs between groups during the study, nonparametric confidence intervals will be constructed based on results of bootstrap analyses. For all test procedures, a probability value of less than 0.05 will be considered as statistically significant.

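### Allocation is stated to be by cluster, but both sample sizes are independent-patient figures, so the stated 80% power at 6 months is not supported

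*Protocol article*

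**What the plan says.** The Abstract and the Study design section both name a cluster design: "A cluster randomized controlled trial will be conducted". Study design adds that allocation within the three Charnley strata is done "by means of cluster randomization to avoid interaction between both patient groups". The unit that forms a cluster, its size and the number of clusters are not given. The setting is a single department: "The study will be conducted at the Orthopedic Department of the UMCG".

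The Sample size section makes two calculations.

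- **Superiority at 3 months.** The target is a gap of 0.254 between the groups in the share who walk without a limp. The calculation is made "with 80% power at a significance level of 0.05 in a one-sided test of a difference between two proportions". It arrives at 50 per group, or 110 in total with 10% dropout. The two underlying proportions are not stated.
- **Non-inferiority at 6 months.** With 0.95 expected in both groups, a margin of 0.10, 80% power and a level of 0.05, it requires 60 per group, or 132 in total with 10% dropout.

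The Statistical analysis section says "Random effect models will be applied for longitudinal analyses" and, for costs, that "nonparametric confidence intervals will be constructed based on results of bootstrap analyses". The non-inferiority interval is described under Sample size. Clusters are mentioned in none of these places.

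**The concern.** When groups of patients are allocated together and their outcomes are correlated, each patient carries less information than an independently allocated one. The variance of the between-group difference grows by the design effect. A sample size computed for independent patients then delivers less than its stated power.

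This matters most at 6 months, where the larger sample size is set and almost nothing is held in reserve. If the analysis also left clusters out, the intervals would be too narrow. In a non-inferiority comparison that error favours the positive claim.

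**Working it through.** **Inputs from the article:** difference 0.254, n = 50 per arm, one-sided 0.05, 80% power (3 months); p = 0.95 in both arms, margin 0.10, n = 60 per arm, level 0.05, 80% power (6 months); dropout 10%.

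**Assumed, because the article gives neither:** equal cluster size m = 2, 4 or 10; ICC = 0.01, 0.05 or 0.10. For 3 months, rates of 0.373 and 0.627, which are symmetric about 0.5 and so nearly the least favourable for this difference.

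**Step 1: reproduce the 6-month figure without clustering.**
n = 2 × 0.95 × 0.05 × (1.645 + 0.842)² / 0.10² = 0.095 × 6.183 / 0.01 = 58.7, so 59 per arm against 60 stated. Then 120 × 1.1 = 132, exactly the stated total, so the only inflation is for dropout. One-sided 0.05 is the level that reproduces 60 (one-sided 0.025 gives 75), and it is used below.

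**Step 2: reproduce the 3-month figure without clustering.**
The pooled two-proportion formula gives (1.645 × 0.7071 + 0.842 × 0.6839)² / 0.254² = 46.9, so 47 per arm. The maximum-variance form gives 48. With a continuity correction and control rates of 0.20 to 0.55 the result is 49 to 55. The stated 50 fits an independent-patient formula, and 100 × 1.1 = 110 again leaves room only for dropout.

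**Step 3: how much design effect can each calculation absorb?**
DE = 1 + (m − 1) × ICC, and effective n = n / DE.

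- 6 months: standard error at n = 60 is √(0.095 / 60) = 0.0398. Power = Φ(0.10 / 0.0398 − 1.645) = Φ(0.868) = 80.7%. It falls below 80% once DE exceeds 60 / 58.7 ≈ 1.02.
- 3 months at 60 completers per arm (the target behind 132): power = Φ((0.254 × √60 − 1.645 × 0.7071) / 0.6839) = Φ(1.176) = 88.0%. It stays at or above 80% up to DE = 60 / 46.9 ≈ 1.28. At the stated 50 per arm it starts at 82.3%.

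**Step 4: the assumed grid.** The last column is the true level of a nominal one-sided 5% test that ignores clusters, 1 − Φ(1.645 / √DE).

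| m | ICC | DE | 6-month power, 60 per arm | 3-month power, 60 per arm | Level if clusters ignored |
|---|---|---|---|---|---|
| 2 | 0.01 | 1.01 | 80.4% | 87.7% | 5.1% |
| 2 | 0.05 | 1.05 | 79.0% | 86.6% | 5.4% |
| 2 | 0.10 | 1.10 | 77.4% | 85.1% | 5.8% |
| 4 | 0.01 | 1.03 | 79.7% | 87.2% | 5.3% |
| 4 | 0.05 | 1.15 | 75.8% | 83.7% | 6.3% |
| 4 | 0.10 | 1.30 | 71.2% | 79.5% | 7.5% |
| 10 | 0.01 | 1.09 | 77.7% | 85.4% | 5.8% |
| 10 | 0.05 | 1.45 | 67.1% | 75.4% | 8.6% |
| 10 | 0.10 | 1.90 | 57.1% | 65.0% | 11.6% |

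Across the same grid, a nominal 95% interval that ignores clusters covers 94.9% down to 84.5%. These are large-sample figures. At m = 10 there would be only about 132 / 10 ≈ 13 clusters, and the few degrees of freedom would lower power further.

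**The case against.** **The analysis may already handle clusters.** A reader might infer that the listed analyses treat patients as independent and that the intervals are therefore too narrow. The text does not go that far. It names random effect models without listing the random effects, and a bootstrap without its resampling unit. A condensed article may leave both to the full plan. This stands: the error inflation above is conditional on clusters being ignored. A cluster term in the analysis would not, however, repair the sample size.

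**ANOVA and chi-square are not evidence.** They too lack a cluster term, but the article limits them to baseline comparisons, so they do not bear on the treatment claims.

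**Power at 3 months may still be adequate.** It is tempting to say the stated power fails at both time points. At the 60 completers per arm aimed for, the 3-month test keeps 80% up to a design effect of about 1.28, so that failure is not shown over much of the grid. The calculation behind 50 per arm still omits clustering.

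**Large design effects may be unrealistic.** From March 2007 to May 2008, 132 patients over 15 months is about 8.8 a month, or about 2.9 per stratum per month if the three strata were equal. A cluster of 10 within a stratum would then span more than three months. All patients are in one department, and anaesthesia, analgesia and physiotherapy are standardised in both groups. No text says that clusters share a surgical team. This stands as a reason not to read 57% as the expected power. It does not show the ICC to be zero, and at 6 months m = 4 with ICC 0.01 is already enough to fall below 80%.

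**The word may be a slip for blocks.** If patients are allocated individually, the design-effect argument falls away. The stated reason for clustering, keeping the two patient groups apart, points to real groups. If it is a slip, the text still needs correcting.

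**Conclusion.** The concern holds, and the article is wrong as written: the stated design and the stated sample size belong to different trials. The firm part is that 60 per arm is the independent-patient number, with a reserve of about 2% in variance, so 80% power at 6 months is not delivered under any design effect above about 1.02.

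The size of the shortfall depends on a cluster size and ICC that the article does not give. Over the assumed grid, 6-month power is about 80% to 57%, with 67% at m = 10 and ICC = 0.05. At very small clusters and a low ICC the loss is trivial (80.4% against 80.7%). Power at 3 months is less exposed, at about 88% without clustering, 84% at m = 4 and ICC = 0.05, and 65% at m = 10 and ICC = 0.10, all at the assumed rates. On the analysis side, what can be said is that no cluster term is stated for the non-inferiority interval, the longitudinal models or the cost bootstrap.

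**What to change.** 1. In Study design, define the cluster unit, its size and the planned number of clusters. If patients are in fact allocated individually or in blocks, replace the word cluster with the correct term; the remaining steps then fall away.
2. If clusters are real, restate in Sample size the 3-month and 6-month power for 132 patients, using the planned cluster size and a stated ICC range.
3. Include cluster in the 3-month comparison, the 6-month risk-difference interval and the longitudinal models, as a random effect or through robust standard errors with a small-sample correction.
4. Resample whole clusters in the cost bootstrap.
5. Keep the cluster identifier in the dataset and report the observed ICC.

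The cost is mostly wording and one extra variable. The downside is wider intervals and a less favourable stated power.
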